### Statistical analysis

The main analysis will be conducted as an intention-to-treat (ITT) analysis for all participants that are included in the study [50]. Pattern of missing data and dropout will be examined and if appropriate multiple imputations will be used based on the nature of the missing data. The primary analysis is to evaluate between group differences in change on ODI scores at 6 months. All statistical tests are carried out at the 5% significance level (two-sided).

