### Recruitment procedures

All participants are recruited through the PCRUs. Individuals with low back pain who contact the PCRU by phone are informed about the study and invited to participate. For individuals who are willing to participate (orally informed consent is given), and who meet the eligibility criteria (assessed by a primary health care staff member), a first (baseline) visit is scheduled at the PCRU. Information about the study will also be sent by email to the participants, after the phone contact and before the first PCRU visit. During the first visit to the PCRU, the participants sign a letter of informed consent before the treatment starts. At each PCRU two study coordinators (chiropractor and physiotherapist) are responsible for the enrolment of participants. Being a pragmatic RCT, there are no criteria for discontinuing or modifying allocated interventions, or improving adherence for a given trial participant. There is also no relevant concomitant care or intervention permitted or prohibited during the trial. The patients have the option to withdraw from the study at any point in time.

The recruitment of participants needs to be carefully monitored for each PCRU without any interaction between researchers and potential study participants. Throughout the study, the study coordinators at each PCRU will be contacted by the first author (FG) on a weekly basis about the enrolment of participants and the recruitment rate. During the start of the study (first 4 weeks) FG also assesses whether the information made available to each PCRU is clear regarding study methods and recruitment procedures. If needed, the information about study methods and recruitment procedures will be updated and clarified. After potential amendments, all PCRUs will continue the recruitment of participants according to the updated procedures. Additionally, FG will meet all the study coordinators on a monthly basis to review and gain feedback on the enrolment procedures and the recruitment rate.

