#### Required sample size

A change of 10 percentage points on the ODI scale is usually defined as the minimal clinically important difference (MCID) [45]. To detect a reduction of 10 percentage points (SD of 15) in the ODI score, which is in agreement with the study of Davidson et al. [45] and Hägg et al. [46], with a two-sided 5% significance level and a power of 80%, a sample size of 150 patients per group will be necessary, given an anticipated dropout rate of 20%. Each PCRU will recruit subjects until the required number is achieved. The enrolment period will extend over 33 months. The projected sample size will provide sufficient statistical power for linear mixed regression and Generalised Estimating Equation (GEE) models considering compound symmetry of the covariance structure and the number of repeated measures [47]. Further, a change of 10–30 percentage points in the NRS scale is usually defined as a MCID [48, 49]. To detect a reduction of 10 percentage points in the NRS, with a two-sided 5% significance level and a power of 80%, a sample size of 146 patients per group will be necessary, given an anticipated dropout rate of 20%.

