#### Primary outcome measure

The primary analysis is to evaluate between-group differences in percentage point change in ODI scores at 6 months compared to baseline. One-way analysis of variance (ANOVA) will be used to evaluate the between-group difference for the primary outcome variable ODI at 6 months. A Levine’s test will be employed to check the assumption of equality of variance for the ANOVA. Assumption of normality will be checked by using skewness and normal probability plot. In case of violation of the normality assumption, we will use the non-parametric Kruskal-Wallis H test which does not require the assumption of normality. If the assumption of homogeneity of variance is violated we will use, the Welch or the Brown and Forsythe test. If the overall ANOVA is significant, we will perform further analysis using a Tukey or Games-Howell post hoc pairwise comparison. We will use Games-Howell if there is a violation of the equality of variance assumption. To evaluate effect size, we will present the difference between means, 95% confidence interval and the partial eta-squared (*η*
^2^).

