#### Secondary outcome measures

Additional analysis of ODI will be done to evaluate the percentage point change in ODI scores and improvement at 3 and 12 months, respectively. Since the trial involves repeated measures data, a linear mixed model will also be used to analyse the secondary outcome measure. To account for repeated measures, to model within-subject variance, and to handle correlated data of continuous variables we will use a linear mixed model. An interaction term will be introduced in the model to examine heterogeneity effect.

The effect of treatment will be evaluated separately for each outcome variable (both primary and secondary) by using a linear mixed model. For binary and ordinal outcome variables a GEE will be employed. The latter model will be used to evaluate the effect of treatment on physical activity at 3, 6, and 12 months.

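### The primary 6-month ODI test covers all participants only if multiple imputation is chosen after the missing data have been inspected, so the stated ITT analysis is not secured

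*Protocol article*

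**What the plan says.** All references are to the protocol article.

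- **Population** (Statistical analysis): "The main analysis will be conducted as an intention-to-treat (ITT) analysis for all participants that are included in the study".
- **Missing data** (same section): "Pattern of missing data and dropout will be examined and if appropriate multiple imputations will be used based on the nature of the missing data". No criterion is attached to the condition.
- **Primary variable** (Statistical analysis, Primary outcome measure): "The primary analysis is to evaluate between-group differences in percentage point change in ODI scores at 6 months compared to baseline".
- **Primary test** (same section): "One-way analysis of variance (ANOVA) will be used to evaluate the between-group difference for the primary outcome variable ODI at 6 months".
- **Planned loss** (Required sample size): "a sample size of 150 patients per group will be necessary, given an anticipated dropout rate of 20" per cent. The figure has no time point and is not split by arm.
- **Withdrawal** (Recruitment procedures): "The patients have the option to withdraw from the study at any point in time".
- **Repeated measures** (Statistical analysis, Secondary outcome measures): "Since the trial involves repeated measures data, a linear mixed model will also be used to analyse the secondary outcome measure". The next paragraph of that section extends the mixed model to every outcome, the primary one included, but as an additional analysis.

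ODI is collected at baseline and at 3, 6 and 12 months. Participants learn their allocation at the first visit, are not blinded, and complete the questionnaire themselves.

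**The concern.** A change score to 6 months exists only where the 6-month value was observed or has been filled in. One-way ANOVA has no means of its own to use a participant who answered at baseline and 3 months and then stopped. Whether the primary test covers everyone in the stated ITT population therefore depends entirely on the imputation decision, and the plan takes that decision only after the pattern of missingness has been looked at.

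Inspection cannot settle the question. It can show that dropout is related to values already recorded. It cannot show that dropout is unrelated to the 6-month ODI that was never seen, so it cannot establish that leaving these participants out is safe.

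Two things are at stake. First, if early response influences who leaves, and does so differently by arm, the complete-case contrast is biased although the trial holds 3-month ODI values that bear on the correction. Second, the primary result is left open to a choice made after data are in hand. Differential dropout is plausible here because patients know their arm, outcomes are self-reported, and one of the four arms receives only information and advice.

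**Working it through.** **1. How many participants depend on the decision.** Planned: 600 in four groups, 150 per group, 20% dropout.

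- Per group: 150 × 0.80 = 120 with data, 30 without.
- Overall: 480 with data, 120 without, if the 20% is read as loss by 6 months.

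**2. Is power the issue?** The stated inputs ("To detect a reduction of 10 percentage points (SD of 15) in the ODI score", two-sided 5%, 80% power) give n = 2 × (1.960 + 0.842)² × 15² / 10² = 35.3, so 36 per group, and 36 / 0.80 = 45 after dropout. The stated 150 is not reproduced. That is a separate matter, but it means 120 per group is ample. The standard error of a pairwise difference is 15 × √(2/120) = 1.94, and power for 10 points is 99.9%. The question is bias and coverage of the ITT population, not power.

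**3. Bias of a complete-case difference.** In each arm let d be the dropout share and g the mean 6-month change of dropouts minus that of completers. The full-arm mean equals the completer mean plus d × g. The complete-case difference (active minus advice) is therefore off by d(advice) × g(advice) − d(active) × g(active). The document gives neither g nor d by arm, so these values are assumptions:

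| Dropout, advice / active | Gap g, advice / active | Shift in difference (points) |
|---|---|---|
| 20% / 20% | 5 / 5 or 10 / 10 | 0 |
| 20% / 20% | 5 / 0 | 0.20 × 5 = 1.0 |
| 20% / 20% | 10 / 0 | 0.20 × 10 = 2.0 |
| 30% / 10% | 5 / 5 | 0.30 × 5 − 0.10 × 5 = 1.0 |
| 30% / 10% | 10 / 10 | 0.30 × 10 − 0.10 × 10 = 2.0 |

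**4. Simulation with an explicit dropout mechanism.** Assumptions: SD of change 15; true active-versus-advice difference −6; correlation of 3- and 6-month change 0.5 to 0.7; odds of dropout 1.5 to 2 times higher per SD of worse 3-month change.

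| Scenario | Complete-case difference | Shift |
|---|---|---|
| 20% in both arms, same mechanism | −6.0 | none |
| 23% vs 17%, non-improvers leaving both arms | −5.8 to −5.6 | 0.2 to 0.4 |
| 30% (advice) vs 10% (active), non-improvers leaving both arms | −5.4 to −4.7 | 0.6 to 1.3 |
| 20% in both arms, response-related in the advice arm only | −5.4 to −4.6 | 0.6 to 1.4 |

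The last row agrees with step 3: shifts of 0.6 to 1.4 at 20% dropout correspond to gaps of 0.6 / 0.20 = 3 to 1.4 / 0.20 = 7 points.

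Imputation by arm from the 3-month ODI returned −6.0 throughout. That is expected, because dropout was made to depend only on the 3-month value. It shows what the method can recover under missing-at-random, not that missing-at-random holds in this trial.

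**The case against.** The protocol nowhere restricts the ANOVA to participants with a 6-month ODI. It states ITT and expressly foresees multiple imputation. A reader might infer that the anticipated 20% will leave the primary analysis. The document does not support that: they leave only if imputation is declined. This limit stands.

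Several features reduce the risk. Data analysts are blinded to allocation (Blinding), which limits steering towards a favoured arm. Only people willing to accept any of the four treatments are enrolled (Characteristics of participants). Up to three reminders go out for each follow-up (Data collection). A mixed model of ODI across visits is already planned and could expose a discrepancy. All of this is fair. But blinding does not remove complete-case bias or turn a choice made after inspection into a fixed one, and the mixed model does not carry the primary conclusion.

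Evidence for arm-related dropout is thin. The Discussion says that unmet preference may affect outcome; it does not mention dropout. The right to withdraw says nothing about who leaves. Equal rates with a common mechanism give no bias, and the moderate shifts are below one standard error (1.94) and well below the 10-point MCID. This stands too, so bias is possible and not demonstrated.

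A reader might also infer that a large part of the treatment effect could be lost. That needs opposite mechanisms, non-improvers leaving advice while improvers leave active care, and nothing in the document supports this pattern. Nor does the point extend to a shortfall in complete 12-month costs and QALYs. The 20% is a dropout rate, not independent loss at each visit, and handling of those components belongs to an analysis plan that is not shown, as does the detail of any imputation model.

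**Conclusion.** The point holds in a limited form. The primary test includes participants without a 6-month ODI only if multiple imputation is chosen, and that choice is conditional and follows inspection of the data. The stated ITT analysis is therefore not secured for about 120 of 600 participants, taking the 20% as loss by 6 months.

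If response-related dropout differs between arms, a complete-case contrast would move by about 0.6 to 1.4 points on an assumed 6-point difference (0.6/6 = 10% to 1.4/6 = 23%) in the two moderate scenarios. It would move by nothing if rate and mechanism are equal. These sizes rest on the assumed SD, correlation, dropout odds and arm split, and the document does not say which case applies. Power is not threatened.

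This is more than detail left to a later plan. The article itself states the conditional rule, and it already plans for ODI a method that would serve better as the primary analysis.

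**What to change.** Replace the conditional clause with a fixed rule for the primary 6-month ODI comparison, in one of two forms:

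- **Mixed model as primary.** Take the 6-month between-group contrasts from the linear mixed model already planned for ODI, fitted to the baseline, 3-, 6- and 12-month values with group-by-visit terms. The overall test of the four groups at 6 months takes the place of the ANOVA, followed by the planned pairwise step.
- **Imputation always applied.** Keep the ANOVA, always preceded by multiple imputation by arm using the other ODI visits.

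Keep the complete-case ANOVA as a sensitivity analysis. Add one sensitivity analysis that departs from missing-at-random by worsening imputed ODI over a stated range, separately by arm.

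The cost is wording and some extra analysis work, with no new data or patients. The primary result then rests on a missing-at-random model, which the last analysis probes. Under the mixed model, participants with no follow-up ODI add little or no information on the 6-month contrast. Because randomisation precedes baseline data collection, some may have no ODI at all. Their number should be reported by arm.

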#### Primary outcome measure

The primary analysis is to evaluate between-group differences in percentage point change in ODI scores at 6 months compared to baseline. One-way analysis of variance (ANOVA) will be used to evaluate the between-group difference for the primary outcome variable ODI at 6 months. A Levine’s test will be employed to check the assumption of equality of variance for the ANOVA. Assumption of normality will be checked by using skewness and normal probability plot. In case of violation of the normality assumption, we will use the non-parametric Kruskal-Wallis H test which does not require the assumption of normality. If the assumption of homogeneity of variance is violated we will use, the Welch or the Brown and Forsythe test. If the overall ANOVA is significant, we will perform further analysis using a Tukey or Games-Howell post hoc pairwise comparison. We will use Games-Howell if there is a violation of the equality of variance assumption. To evaluate effect size, we will present the difference between means, 95% confidence interval and the partial eta-squared (*η*
^2^).

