#### Primary outcome measure

##### Oswestry Disability Index (ODI) − A measure of back pain-related functional limitation

The ODI is a condition-specific instrument that measures back pain-related functional limitation [30]. It consists of ten questions where each question has six response choices and the value of each question ranges from 0 (no problems) to 5 (worst imaginable problems). A total ODI score is computed as the sum of scores on each question, and the total score of ODI varies between 0 (no problems) and 50 (worst imaginable problems). The total ODI score is then normalised to 0–100, by multiplying the (unadjusted) total score by 2. The ODI normalised score, based on the ODI outcome measure at 6 months, is our primary outcome measure [12]. The ODI has a high reliability, validity, and responsiveness, and is easy to administrate and is sensible to find clinical changes in treatment of patients with CLBP [34, 35].

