#### Baseline

Baseline data will be collected during the first visit or at 1–4 days before the first visit at the PCRU. Data on individual characteristics (age, sex, education, smoking status, physical activity, use of pain killers, and pain duration), outcome measures (back pain-related functional limitation, pain intensity, general health, HRQoL, working status) and resource consumption (pharmaceuticals, health care visits, clinical examinations, and hospital days) are collected.

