#### Additional analysis for percentage point change in ODI

Two additional analyses will be carried out for the primary outcome variable ODI at 6 months. First, an adjusted analysis will be used to control for baseline variables (age, sex, education, smoking status, physical activity, use of pain killers). This multiple linear regression analysis will adjust for potential predictor variables which might reasonably be expected to be predictive of favourable outcomes. We will perform residual analysis to assess model assumptions and goodness-of-fit. Secondly, a subgroup analysis will be performed to detect differences between groups of patients with an ODI normalised score at baseline either less than 40% or equal to or greater than 40% [12].

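### The primary ODI analysis makes no covariate adjustment for baseline ODI, and the supporting adjusted regression omits it too, which costs precision and leaves chance baseline imbalance badly handled

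*Protocol article*

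**What the plan says.** Under Statistical analysis, Primary outcome measure, the aim is to compare "between-group differences in percentage point change in ODI scores at 6 months compared to baseline". The next sentence names the test: "One-way analysis of variance (ANOVA) will be used to evaluate the between-group difference for the primary outcome variable ODI at 6 months". The fallbacks (Kruskal-Wallis, Welch, Brown and Forsythe) and the post hoc comparisons (Tukey, Games-Howell) carry no covariates either.

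Under Additional analysis for percentage point change in ODI, a multiple linear regression will "control for baseline variables (age, sex, education, smoking status, physical activity, use of pain killers"). Baseline ODI is not in that list. The same section uses it only to form a subgroup split, "groups of patients with an ODI normalised score at baseline either less than 40% or equal to or greater than 40" per cent.

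Baseline ODI is available. The Baseline section lists "outcome measures (back pain-related functional limitation, pain intensity, general health, HRQoL, working status") among the data collected, and functional limitation is measured by the ODI.

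Under Outcome measurements, the primary outcome reads as a score at one time point: "The ODI normalised score, based on the ODI outcome measure at 6 months, is our primary outcome measure".

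The Secondary outcome measures part of the analysis section adds a linear mixed model for every outcome, the primary one included, without naming a baseline ODI term. Required sample size uses this target: "To detect a reduction of 10 percentage points (SD of 15) in the ODI score". It does not say whether the SD is that of the score or of the change.

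**The concern.** A patient's ODI before treatment can be expected to predict ODI six months later. An analysis that estimates that relation removes the predictable part of the outcome variance. The planned analyses do not. A one-way ANOVA of change fixes the slope on baseline at 1; a one-way ANOVA of the 6-month score fixes it at 0. Unless the true slope equals the fixed value, the contrast has more variance than it needs, and an arm that starts higher or lower by chance shifts the result.

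The supporting regression does not repair this, because its six covariates are no substitute for baseline ODI. The omission also sits badly with that section's own aim of adjusting for likely predictors of outcome.

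The loose naming of the primary variable adds to the problem. Score and change give different unadjusted ANOVA results and respond to baseline imbalance in opposite directions.

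**Working it through.** **Inputs.** From Required sample size: difference 10 points, SD 15, two-sided 5%, power 80%, 150 per group, 20% dropout, hence 150 × 0.8 = 120 completers per group. The article gives no correlation rho between baseline and 6-month ODI, so rho is an assumption, shown from 0.3 to 0.8. SDs at the two times are assumed equal (s) unless stated otherwise.

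**The plan's own figure.** 2 × (15/10)² × (1.960 + 0.842)² = 35.3, so 36 per group, and 36/0.8 = 45 after dropout. The stated 150 does not reproduce. That is a separate matter; here it only shows how much room there is. With 120 completers, SE = 15 × √(2/120) = 1.94, power for 10 points is about 99.9%, and the difference detectable with 80% power is 1.94 × 2.80 = 5.4 points.

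**Variance of the contrast, up to the common factor 2/n.**
- Change score: 2s²(1 − rho)
- 6-month score: s²
- ANCOVA: s²(1 − rho²)

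ANCOVA over change is (1 − rho²)/[2(1 − rho)] = (1 + rho)/2. ANCOVA over 6-month score is 1 − rho².

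| Assumed rho | ANCOVA / change | Extra patients the change score needs | ANCOVA / 6-month score | Completers under ANCOVA that match 120 under change |
|---|---|---|---|---|
| 0.3 | 0.65 | 54% | 0.91 | 78 |
| 0.5 | 0.75 | 33% | 0.75 | 90 |
| 0.7 | 0.85 | 18% | 0.51 | 102 |
| 0.8 | 0.90 | 11% | 0.36 | 108 |

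The direction does not need equal SDs. With SDs s0 and s1, the change-score variance minus the ANCOVA variance is (s0 − rho·s1)², which is never negative.

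**In ODI points.** At rho 0.5 the detectable difference falls from 5.4 to 5.43 × √0.75 = 4.7. This holds whether SD 15 is the SD of the score or of the change, since 15 × √(2 × 0.5) = 15. If SD 15 is the SD of change, power for a 5-point difference with 120 per arm rises from 73% to 89%, 85%, 80% and 78% at rho 0.3, 0.5, 0.7 and 0.8.

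**Chance imbalance.** If one arm starts d points higher, the expected shift is (rho − 1)d for the change contrast and rho·d for the 6-month score. For d = 3:

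| Assumed rho | Change score | 6-month score |
|---|---|---|
| 0.3 | −2.1 | +0.9 |
| 0.5 | −1.5 | +1.5 |
| 0.7 | −0.9 | +2.1 |
| 0.8 | −0.6 | +2.4 |

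For scale, if the baseline SD is 15, the SE of a baseline difference between two arms of 150 is 15 × √(2/150) = 1.73. Three points is thus about 1.7 SE, and a one-SE imbalance at rho 0.5 shifts the change contrast by about 0.9 points.

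**Score or change.** Fit 6-month ODI on treatment and baseline, with slope b on baseline. Subtracting baseline from both sides gives the model for change, with slope b − 1 and the same treatment coefficient. With baseline ODI as covariate, the choice between the two variables no longer alters the treatment effect.

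**The case against.** The strongest reply is that the planned test is sound. Under randomisation a change-score ANOVA is unbiased over repeated randomisations and keeps its type I error. A reader might infer that the primary test is invalid; the article gives no ground for that. A reader might also infer that the trial is underpowered as a result. It is not: the fall from 5.4 to 4.7 points lies wholly below the stated 10-point target. Both replies stand and limit the point to efficiency and conditional bias.

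It would also be too strong to say that the plan leaves baseline imbalance uncorrected. That is true only of an ANOVA on the 6-month score. The stated aim of the primary analysis is change, and the additional-analysis section, headed as change, uses ODI at 6 months as what looks like shorthand for it. For change, the fault is over-correction.

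The planned mixed model is a partial answer. It covers the primary outcome, and an article may leave its terms to the analysis plan. But it is placed among the secondary analyses and names no baseline ODI covariate, so it does not change the primary result.

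Baseline ODI cannot be assumed present for every randomised patient. The Randomisation section has the envelope opened during the phone call, and the questionnaire comes later, at the first visit or one to four days before it. Allocation is revealed at that visit, so some baselines could follow disclosure. Change scores share both weaknesses.

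Finally, one might ask for rehabilitation unit and pain duration in the model as well. The article describes no stratification by unit and does not show that pain duration is prognostic, so it supports neither demand.

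**Conclusion.** The point holds as one of precision and conditional bias. The named primary test has no covariate, and the explicit list in the supporting regression omits baseline ODI. These are choices the article states, not detail left for later. Assuming equal SDs, adjustment cuts the variance of the contrast by 35%, 25% and 15% at rho 0.3, 0.5 and 0.7, and by 10% at 0.8. The size depends on a correlation that the article does not give; the direction does not.

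Planned power for 10 points at SD 15 is unaffected. The benefit lies in narrower confidence intervals and in smaller contrasts, notably those between active arms, which the second research question compares. The shift between score and change is loose wording rather than a clear contradiction, and the same edit makes it harmless. The change should be made before analysis, but the analysis as planned would not be wrong without it.

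**What to change.** - Make the primary analysis an ANCOVA of 6-month ODI on treatment group with baseline ODI as covariate. The 6-month contrast from the planned mixed model, adjusted for baseline ODI, would serve equally.
- Name the primary variable in the same words in the outcome and analysis sections.
- Take the overall test and the pairwise comparisons from that model, with multiplicity adjustment. Apply the assumption checks to its residuals, and say what replaces the present rank-based and unequal-variance fallbacks (for example, heteroscedasticity-robust standard errors).
- Add baseline ODI to the supporting regression.
- State how participants without a baseline ODI are handled.
- Keep the unadjusted ANOVA as a sensitivity analysis.

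No new data are needed, since baseline ODI is already in the questionnaire. The cost is more than a line in an analysis plan: the ANOVA, its fallbacks and its post hoc tests are written into the protocol, so that section has to be amended, before the data are analysed.

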In Sweden, patients with low back pain are often treated by either chiropractors or physiotherapists. Sometimes patients are treated by chiropractors and physiotherapists in collaboration. Besides providing general information and advice, these occupational groups usually recommend exercise (mostly recommended by physiotherapists) and manual therapies (mostly recommended by chiropractors) [7]. These treatment alternatives are also recommended in guidelines in different parts of the world [27]. As noted above, although a wide range of treatments exist for CLBP, the scientific basis to recommend the use of one treatment alternative over another is limited. There is, therefore, a need for well-designed clinical trials investigating both the effectiveness and cost-effectiveness of treatments for CLBP. Cost-effectiveness studies may provide valuable information on whether it is good value for money to use treatments and examinations provided by chiropractors and/or physiotherapists, in addition to only providing information and advice. Information both about the cost-effectiveness and effectiveness of treatments for CLBP is crucial for decisions aiming at improving the efficiency in the allocation of limited resources for the treatment of CLBP. The results from our study will improve the basis for health care decision-making and policy recommendations and should be considered when producing and updating evidence-based guidelines and recommendations on which treatment strategies to use for CLBP.

The aim of the study is to evaluate the effectiveness (back pain-related functional limitation, back pain intensity, general health, HRQoL, and working status), costs (medical costs and costs for production losses) and cost-effectiveness of chiropractic care and physiotherapy when added to information and advice in the treatment of patients with non-specific CLBP in Sweden.

Research questions:How do chiropractic care and physiotherapy, chiropractic care, or physiotherapy, when added to information and advice, impact outcomes (back pain-related functional limitation, back pain intensity, general health, HRQoL, and working status) as compared with only information and advice?Which (if any) of chiropractic care and physiotherapy, chiropractic care, or physiotherapy, when added to information and advice, is a cost-effective treatment strategy when compared to each other, and when compared with only information and advice?

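### The primary test can switch from ANOVA to Kruskal-Wallis on an informal look at the outcome data, although the plan defines and reports a difference in means

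*Protocol article*

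**What the plan says.** All of this stands in the Protocol article, Statistical analysis, under Primary outcome measure, unless noted.

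- The primary analysis concerns between-group differences in the change in ODI from baseline to 6 months. The test is named: "One-way analysis of variance (ANOVA) will be used to evaluate the between-group difference for the primary outcome variable ODI at 6 months".
- The normality check is: "Assumption of normality will be checked by using skewness and normal probability plot". No cut-off is attached to it.
- The consequence of a failed check is: "In case of violation of the normality assumption, we will use the non-parametric Kruskal-Wallis H test".
- Unequal variance has its own branch: "If the assumption of homogeneity of variance is violated we will use, the Welch or the Brown and Forsythe test".
- Pairwise testing is conditional: "If the overall ANOVA is significant, we will perform further analysis using a Tukey or Games-Howell post hoc pairwise comparison".
- Whichever branch is taken, the effect measure is the same: "we will present the difference between means, 95% confidence interval and the partial eta-squared".

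In the Background, research question 1 asks about each of the three active strategies "as compared with only information and advice". Research question 2, on cost-effectiveness, also compares the strategies with each other. The Blinding section states that outcome assessors and data analysts do not know the allocation.

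**The concern.** The plan defines its target as a difference in mean change and promises to report one. The p-value that decides the trial may nevertheless come from a rank test with a different null hypothesis. Kruskal-Wallis asks whether the four distributions coincide, against the alternative that values in one arm tend to be larger than in another. It reduces to a comparison of location only when the arms share one shape and spread.

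ODI change is derived from a score bounded at 0 and 100. A treatment that helps some patients a great deal and others not at all can change shape and spread as well as the mean. In that situation the primary p-value and the reported mean difference could point to different conclusions.

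Because the check has no threshold, two careful analysts could also choose different primary tests from the same data.

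**Working it through.** **Inputs.** Required sample size gives 150 per group, 20% dropout and an SD of 15 ODI points. Evaluable per arm: 150 × 0.80 = 120. The plan gives no operating characteristics for its test-selection rule, so there is no figure of its own to reproduce. The distribution shapes below are assumptions, because the document gives none.

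**Step 1: rejection rate when all four means are equal.** Simulated trials, 120 per arm, nominal level 5%. The last column applies the plan's rule with an assumed cut-off: absolute skewness of the pooled residuals above 0.5 leads to Kruskal-Wallis; otherwise a Levene p below 0.05 leads to Welch; otherwise ANOVA.

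| Arms (equal means) | Kruskal-Wallis | ANOVA | Welch | Rule with assumed cut-off |
|---|---|---|---|---|
| A. Four normal, SD 15 | 4.6% | 4.6% | 4.4% | 4.7% |
| B. Four identical gamma (shape 2), SD 15 | 4.9% | 4.5% | 4.8% | 4.9% |
| C. Three normal, one gamma (shape 1.5), SD 15 | 13.1% | 5.3% | 5.7% | about 8% |
| D. Three gamma (shape 2), one mirrored, SD 15 | 42.5% | 4.7% | 5.2% | 34.2% |
| E. Gamma (shape 2), SD 12, 15, 18, 22 | 30.5% | 5.9% | 5.6% | 30.5% |

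Rows A, B, D and E use 5,000 trials. Row C uses 4,000, and its last column comes from a repeat with 6,000. Repeats with other seeds moved row C between about 12.5% and 14%, and row E between about 28% and 30%. The summary range of 12% to 34% takes Kruskal-Wallis itself in rows C and E, and the rule as a whole in row D. If row D always went to Kruskal-Wallis, its figure would be 42.5%.

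In row C the rule rejects less often than Kruskal-Wallis alone because the switch is often not triggered. A gamma with shape 1.5 has skewness 2/√1.5 = 1.63, and one such arm in four gives pooled skewness of about 1.63/4 = 0.41, below the assumed 0.5.

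**Step 2: is the switch needed?** A gamma with shape 2 has skewness 2/√2 = 1.41. The mean of 120 such values has skewness 1.41/√120 = 0.13, which is close to normal. Row B agrees: ANOVA and Welch hold their level under marked common skew.

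**Step 3: the omnibus gate and the size of the family.** SE of a pairwise difference = 15 × √(2/120) = 1.94. Critical |t| (476 df): Tukey over six pairs 2.578, Dunnett over three contrasts 2.357. Ungated power ≈ Φ(difference/SE − critical value). For 10 points: 10/1.936 = 5.164, so Tukey is Φ(2.586) = 99.5% and Dunnett Φ(2.807) = 99.7%. Simulated power (300,000 runs) for one active arm against advice:

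| True difference | Gated Tukey | Ungated Tukey | Dunnett |
|---|---|---|---|
| 10 (planned) | 99.5% | 99.5% | 99.7% |
| 6 (assumed) | 69.5% | 69.8% | 77.0% |
| 5 (assumed) | 49.5% | 50.1% | 58.9% |
| 5, other two active arms 2.5 (assumed) | 47.9% | 50.2% | 58.9% |

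The gate costs from 0 to 50.2 − 47.9 = 2.3 percentage points. The rest of the gap comes from adjusting for six pairs rather than three.

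**The case against.** The strongest reply is that nothing goes wrong when treatment has no effect at all. Randomised arms then share one distribution, and Kruskal-Wallis, ANOVA, Welch and the selection rule all hold about 5% (rows A and B). Rows C to E are constructed, and row C shows that the switch may not even be triggered. Mean differences are reported on every branch, and the plan adds an adjusted regression and a linear mixed model for ODI. All of that stands. It does not remove the mismatch, because the p-value labelled primary can still test something other than the mean difference beside it.

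It can also be said that a cut-off, an order for the two checks and a post hoc test after Kruskal-Wallis belong in an analysis plan that is not shown. That is fair, and their absence is not the point. The point is the rule that the article does state.

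Four stronger readings are tempting and are not supported:

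- **That the test is chosen after unblinding.** The Blinding section keeps analysts blinded, and all the checks can be run on coded arms. What holds is that the choice follows sight of the outcome data.
- **That power for research question 1 is materially lost.** At the plan's own 10 points and SD 15 the comparison is 99.5% against 99.7%. The larger gaps need true differences of 5 to 6 points, which the document does not assume.
- **That all-pairs testing is an error.** The primary analysis asks for between-group differences in general, research question 2 compares arms with each other, and Tukey controls the familywise error.
- **That the tests cannot be combined with multiple imputation.** The plan makes imputation conditional ("if appropriate multiple imputations will be used based on the nature of the missing data"), so this is speculative.

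**Conclusion.** The concern holds for the Kruskal-Wallis branch. The stated rule can move the primary test away from the mean difference that the plan defines and reports, on an informal check of the outcome data, and the pairwise tests it names do not match that branch. Where means are equal but shape or spread differs, this route can reject about 12% to 34% of the time, against about 4% to 6% for ANOVA or Welch. Those figures rest on assumed gamma shapes and are not a forecast for this trial. A reader might infer a general inflation of type I error, but identical distributions show none. The same result shows that the switch buys no needed protection at about 120 evaluable per arm.

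The omnibus gate is a minor, avoidable cost of 0 to about 2 percentage points of power. Dunnett against Tukey is a design trade-off, not a fault.

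**What to change.** In Statistical analysis, Primary outcome measure:

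1. Name one mean-based primary analysis of change in ODI from baseline to 6 months, with no data-driven switch. Either Welch ANOVA with Games-Howell, or one linear model with heteroscedasticity-robust standard errors and multiplicity-adjusted contrasts, would do. Both keep the change score as the outcome.
2. Report multiplicity-adjusted mean differences with 95% confidence intervals from that same analysis.
3. Remove the condition that pairwise comparisons follow only a significant overall test. Tukey and Games-Howell do not need it for familywise control.
4. Keep Kruskal-Wallis as a sensitivity analysis only.

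Optional: restrict the primary family to the three contrasts with information and advice, Dunnett-adjusted. This gains about 0.2 percentage points of power at 10 points and SD 15, and about 7 to 11 if true differences are 5 to 6 points (an assumption). The price is that active-versus-active pairs become secondary.

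The cost is wording alone, with no extra patients, visits or data. The Timeline places analysis in 2021 and 2022, after data collection is expected to end on 31 December 2020, so the change can be settled before outcomes are analysed.
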